### Power calculation

Appropriate sample size is estimated using Gpower v.3.0.5 software [34]. This calculation is based on the primary outcome measure (alcohol consumption), in a one-way ANOVA test design. Based on [10] we expect an effect-size of *d *= 0.40 when comparing waiting list control and treatment groups. To be able to detect even smaller differential effects (*d *= 0.25) between SOA en TOA with *α *= .05 and *β *= .20, we aim to include 150 participants. The power calculation is summarized in Table 3.

**Table 3 T3:** Power analysis

F tests – ANOVA: Fixed effects, omnibus, one-way		
Analysis:	A priori: Compute required sample size	
Input:	Effect size f	0.25
	α error probability	0.05
	Power (1-β error probability)	0.80
	Number of groups	3
Output:	Non-centrality parameter λ	9.938
	Critical F	3.054
	Numerator df	2
	Denominator df	156
	Total sample size	159
	Actual power	0.805

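### The sample size is claimed to detect d = 0.25 between SOA and TOA with 80% power, but Table 3 used Cohen's f = 0.25; power for that contrast is about 24%

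*Protocol article*

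**What the plan says.** All the statements below come from the protocol article, section Power calculation, unless another section is named.

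- For treatment against waiting list: "we expect an effect-size of *d *= 0.40 when comparing waiting list control and treatment groups".
- For the two treatments, the stated aim is to detect "even smaller differential effects (*d *= 0.25) between SOA en TOA", followed by "with *α *= .05 and *β *= .20, we aim to include 150 participants".
- On method: "This calculation is based on the primary outcome measure (alcohol consumption), in a one-way ANOVA test design".
- Table 3, offered as the summary of this calculation, is headed "F tests – ANOVA: Fixed effects, omnibus, one-way". Its inputs are effect size f = 0.25, alpha 0.05, power 0.80 and 3 groups. Its outputs are lambda 9.938, critical F 3.054, df 2 and 156, total N 159 and actual power 0.805.
- The Randomization section sets 50 participants per arm.
- TOA against SOA on alcohol consumption is part of the first research question (Q1a). The Hypotheses section predicts a significantly larger reduction with TOA at three months.

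**The concern.** The number 0.25 is a d in the text and an f in the table. The text cannot mean f, because it calls 0.25 smaller than d = 0.40. The two indices are on different scales: for two equal groups f is half of d.

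The test is also different. The text speaks of one pairwise contrast, but Table 3 powers an omnibus test of three means, which can be significant only because the waiting list differs from both treatments.

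The 80% is therefore attached to a contrast and an effect size that were not the ones calculated. SOA versus TOA is a leading comparison, since it asks whether counsellor contact adds anything to self-help. At the stated effect, roughly three trials in four of this size would miss it. A reader who trusts the 80% could then take a non-significant result as evidence that counselling adds nothing.

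**Working it through.** **Inputs.** From Power calculation: d = 0.25 (SOA–TOA), d = 0.40 (waiting list against treatment), f = 0.25, alpha 0.05, power 0.80 and N = 159. From Randomization: n = 50 per arm. Assumptions: two-sided pairwise test (sidedness is not stated), complete data, no baseline adjustment. The last matches the section's own one-way ANOVA design.

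**1. Reproduce Table 3.** For a one-way ANOVA, lambda = N × f² with df 2 and N − 3.
- N = 159: lambda = 159 × 0.0625 = 9.9375; critical F(2, 156) = 3.054; power = 0.805. Every printed output matches, so f = 0.25 really was the input.
- N = 150 (the planned number): lambda = 9.375; power = 0.780.

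**2. Convert f = 0.25 to d.** f is the SD of the arm means divided by the within-arm SD.
- Two groups: d = 2f = 0.50.
- Three groups, two arms equal: largest d = 3f/√2 = 0.53.
- Three groups, third arm midway: largest d = f√6 = 0.61.

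**3. Power for the stated contrast.** Two-sample t-test with non-centrality d√(n/2) and 2n − 2 df. For n = 50, √(n/2) = 5 and the critical t on 98 df is 1.984.

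| Comparison | n per arm | Non-centrality | Power |
|---|---|---|---|
| d = 0.25 | 50 | 1.25 | 23.6% |
| d = 0.25 | 53 (Table 3's N) | 1.29 | 24.7% |
| d = 0.40 | 50 | 2.00 | 50.8% |

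- Smallest d with 80% power at n = 50: 0.566 (non-centrality 2.83).
- n per arm for 80% power: 253 at d = 0.25 (759 over three equal arms) and 100 at d = 0.40.
- 95% CI half-width for a pairwise d at n = 50: about 1.96 × √(2/50) = 0.39, wider than the 0.25 target.

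**4. Variants for SOA–TOA at d = 0.25, n = 50.**
- Error variance pooled over three arms: 23.7%.
- One-sided test: 34.3%.
- Omnibus test with a largest difference of 0.25 SD: 18% to 23% at N = 150.

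**5. Omnibus test under patterns suggested by the text, N = 150.**
- Means 0 / 0.40 / 0.65 (waiting list, SOA, TOA): f = 0.268, power 84%.
- Means 0 / 0.40 / 0.40: f = 0.189, power 52%.

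**The case against.** Three arguments can be made for the plan.

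**The omnibus test is adequate under the stated effects.** If SOA lies 0.40 above the waiting list and TOA a further 0.25 above SOA, the omnibus test has 84% power at N = 150. That is correct, but most of the power comes from the waiting-list difference. SOA–TOA stays near 24%, and the text attaches beta = .20 to that contrast.

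**The planned analysis is repeated measures, which can gain precision.** The document does not say whether d is standardised on raw or change scores, and it gives no correlation. Taking d on the raw scale with 50 per arm, power at assumed baseline–follow-up correlations is:

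| Correlation | d = 0.25, baseline-adjusted | d = 0.25, change score | d = 0.40, baseline-adjusted | d = 0.40, change score |
|---|---|---|---|---|
| 0.5 | 30% | 24% | 63% | 51% |
| 0.7 | 41% | 36% | 79% | 72% |
| 0.8 | 54% | 50% | 91% | 88% |

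For d = 0.25, a correlation of about 0.9 is needed to reach 80%. The SOA–TOA conclusion survives this objection. The 51% figure for d = 0.40 is more fragile and needs its assumptions stated.

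**No explicit 80% is claimed for d = 0.40.** This is formally right. The text only expects that effect "when comparing waiting list control and treatment groups", and it could mean both treatments pooled; 100 against 50 at d = 0.40 has 63% power. Calling d = 0.25 smaller still does imply that 0.40 is covered, but this part of the criticism is secondary.

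It is also fair to say that Table 3 is correct for its inputs, that these figures concern alcohol consumption and not the secondary outcomes or treatment response, and that nothing in the article says a null result will be read as equivalence.

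**Conclusion.** The concern holds. The article states 80% power for d = 0.25 between SOA and TOA, and the calculation it cites addresses a different effect-size scale and a different test. With 50 per arm, power for the stated contrast is about 24%, and the detectable difference at 80% power is d = 0.57, more than twice the stated target.

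These figures assume a two-sided 5% unadjusted comparison with complete data. Baseline adjustment would raise them, but not to 80% without a correlation near 0.9 that the document does not state. Loss to follow-up, which the article itself names as a threat, would lower them. For one treatment arm against the waiting list at d = 0.40, the same assumptions give about 51%.

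**What to change.** In the Power calculation section and Table 3:

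1. Delete the claim that 150 participants suffice to detect d = 0.25 between SOA and TOA with 80% power.
2. State that Table 3 concerns the omnibus three-arm test, and that f = 0.25 corresponds to a largest pairwise d of about 0.53 to 0.61 (0.50 in a two-group comparison).
3. Give pairwise figures for 50 per arm, labelled as two-sided, unadjusted and complete data: about 24% power at d = 0.25, about 51% at d = 0.40 for one treatment arm against waiting list, and a detectable d of 0.57 at 80% power. If a gain from baseline adjustment is claimed, state the assumed correlation and show a range.
4. While the table is open, reconcile its N of 159 with the target of 150, where the same omnibus test has 78% power.

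It would also help to say that SOA–TOA will be reported with its 95% confidence interval and that non-significance will not be read as equal effectiveness. Recasting SOA–TOA as an estimation contrast is optional. It would mean rewording the Hypotheses section, which predicts a significant difference.

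The cost of items 1 to 4 is wording and one recalculated table. The stated power becomes less favourable, but no extra participants and no design change are needed.

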### Randomization

After the t0 measurement is completed, participants are allocated to one of the three trial arms. Because this randomized clinical trial is internet-based, we will organize the allocation procedures online as well. As the number of participants we aim to include in each trial arm (*n *= 50) is not very large, random variation in baseline characteristics could reduce group equivalence. Online, server-based performance of randomization procedures comes with the advantage of being able to implement stratified allocation or allocation through adaptive randomization relatively easy.

To prevent between-group variability on relevant baseline characteristics, we use an adaptive or biased-coin randomization algorithm for this trial. Adaptive randomization aims to ensure trial arms are balanced with respect to a priori defined participant factors as well as for the number of participants in each group. Simulation studies show that adaptive randomization provides better balanced trial arms when compared with 'normal' randomization [35] and that it is more efficient in balancing multiple poli-level factors than permutated block stratification [36]. Although not widely used due to organizational complexity, adaptive randomization is a highly effective allocation method, and its wider adaptation in the conduct of randomized clinical trials is recommended [37]. The use of adaptive randomization is supported in the CONSORT statement [38]. We will implement the Pocock & Simon Range Method of adaptive randomization [39], with D = 'range', G is the sum of D (no factor weighting), and P = 0.60.

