### Maximize response rates

Drop-out is a potential threat in every clinical trial. Since attrition rates for online trials tend to be larger than in regular ones [52], we will make extra efforts to maximize response rates. Following suggestions for successful strategies to maximize response rates [41,42], we made follow-up questionnaires as short as possible and give participants feedback on the actual length and their proceedings while filling out the questionnaire. We motivate participants to fill out the questionnaires by sending them a reminder if they do not respond within five days after the first emailed invitation. To optimize a feeling of worthiness and to reward participants for their efforts and time, participants will receive gift coupons (€15,-) after filling out a follow-up questionnaire. Participants will be aware of this incentive upon reading the informed consent form. However, participants who do not fill out the questionnaires after a reminder is sent will be contacted by a call centre. Since 2005, this call centre has been collecting regular outcome data of outpatient addiction treatment for SATCs nationwide in the Netherlands. It is experienced in maximizing response rates in hard to reach populations [43]. For this research project, they will collect outcome data by phone from trial participants who do not respond to emailed invitations. All participants are aware of these procedures, provide phone numbers, and consent with receiving phone-calls for follow-up measurements.

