A second potential risk in this trial would concern the inclusion of participants. The inclusion of enough participants is not our main sorrow. As SOA in the regular context and without promotional efforts is able to attract over 150 new participants each month [6], we think we will manage to include 150 participants in a one year inclusion period. However, the resemblance of the regular online clientele is our main focus of attention. Due to the high accessibility of online help in the normal context and the relatively high constraints posed on participants in this trial, there is a potential risk that the trial participants do not resemble the regular e-clientele exactly. Whether this actually occurs or not can only be answered afterwards, by comparing data on characteristics of trial participants and regular online clientele data.

A third possible limitation concerns integrity of our collected data. As our t0 and t1/t2 data is self reported without a researcher nearby to oversee data-collection, we rely heavily on the correctness of our participants' answers. Various authors evaluate the self-reported data in alcohol research as reliable [53-55]. Tourangeau and colleagues even concluded that self-reported data is more reliable in the absence of a research confederate [56]. However, as an extra means to check data integrity, we included a social desirability scale, to measure whether these tendencies occur in our research population.

Another point of concern on data integrity in this trial could be made about our suggested statistical procedures. Multivariate statistics relies considerably on data distribution normality [57]. As the distribution of alcohol consumption count data is usually zero-elevated and highly skewed, particularly in subjects with alcohol dependence [58], multivariate statistics and most statistical tests should be used with caution. To prevent possible in- or deflated α's, we will use bootstrap methods and permutation tests as suggested by Hesterberg and colleagues [59], to minimize the influence of data distributions on our testing results, if data turn out to be non-normally distributed.

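### The target of 150 falls below the 159 that Table 3 requires, no loss is allowed for, and the stated 80% power for SOA against TOA at d = 0.25 is about 24%

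*Protocol article*

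**What the plan says.** All of this is in the Methods and Discussion of the protocol article.

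- **Power calculation, text.** The expected effect of treatment against waiting list is d = 0.40. The trial is then said to be sized for a smaller SOA–TOA difference, d = 0.25, at α = .05 and β = .20: "we aim to include 150 participants. The power calculation is summarized in Table 3". The test is named: "This calculation is based on the primary outcome measure (alcohol consumption), in a one-way ANOVA test design".
- **Power calculation, Table 3.** This is an a priori calculation of required size for a fixed-effects omnibus F test. The inputs are "Effect size f 0.25", α 0.05, power 0.80 and 3 groups. The outputs are λ 9.938, critical F 3.054, degrees of freedom 2 and 156, actual power 0.805, and a "Total sample size" of 159.
- **Randomization.** This section gives n = 50 as "the number of participants we aim to include in each trial arm".
- **Discussion.** The target is repeated: "we think we will manage to include 150 participants in a one year inclusion period".
- **Maximize response rates.** Extra effort on follow-up is justified as follows: "Since attrition rates for online trials tend to be larger than in regular ones". The Discussion also lists attrition as a threat to the trial. The measures described are reminders, gift coupons, a call centre, a long baseline questionnaire before randomisation, and multiple imputation. No loss rate is given and nothing is added to the sample size.

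**The concern.** Three things do not fit together. First, the text cites Table 3 as the basis for 150, but the table asks for 159, and nothing explains the reduction. Because 150 appears in three sections, it is the working target and not a misprint. Second, the formula behind Table 3 assumes an outcome from every participant, so 159 is a number to be analysed. A trial that expects unusual attrition would normally recruit more than that, and this one recruits fewer. Third, the β = .20 in the text belongs to a two-arm difference of d = 0.25, while the table concerns a three-arm omnibus effect of f = 0.25. These are different quantities.

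What is at stake is how the results are read. TOA against SOA on alcohol consumption is part of research question Q1a and carries a directional hypothesis. If the comparison is not significant, a reader who trusts the stated 80% power may conclude that counsellor contact adds nothing of the size d = 0.25. The trial could not support that conclusion.

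**Working it through.** **Inputs from the article:** 3 equal arms, f = 0.25, α = 0.05, target power 0.80, required N = 159, planned N = 150 (3 × 50), and SOA–TOA d = 0.25. **Assumed, because the article gives no rate:** loss of 10% to 40%.

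**1. Reproduce Table 3.** For the one-way omnibus test, λ = N·f², df = (2, N − 3), and power = P(F′ > F_crit), where F′ is non-central F with parameter λ. At N = 159, λ = 159 × 0.0625 = 9.9375, df = (2, 156), F_crit = 3.054 and power = 0.805. Every output line of the table is matched. With equal arms, 156 gives 0.797, so 159 (53 per arm) is the smallest adequate size.

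**2. Put in the planned number.** At N = 150, λ = 150 × 0.0625 = 9.375, df = (2, 147), F_crit = 3.058 and power = 0.780. So β is 0.22, not 0.20. The shortfall is 9 participants (9/159 = 5.7%).

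**3. Allow for loss.** Analysed N = 150 × (1 − loss):

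| Assumed loss | Analysed N | λ | Omnibus power | Recruits needed to analyse 159 |
|---|---|---|---|---|
| 0% | 150 | 9.375 | 0.780 | 159 |
| 10% | 135 | 8.438 | 0.732 | 177 |
| 20% | 120 | 7.500 | 0.676 | 199 |
| 30% | 105 | 6.563 | 0.612 | 228 |
| 40% | 90 | 5.625 | 0.540 | 265 |

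The last column is 159/(1 − loss), rounded up. Multiple imputation can reduce bias from missing outcomes, but it does not in general put back the information they would have carried. It does not replace an allowance.

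**4. The SOA–TOA claim.** For two equal groups f = d/2, so f = 0.25 corresponds to d = 0.50, twice the difference named in the text. For a two-sided t test at 0.05 with n per arm, the non-centrality is d·√(n/2) on 2n − 2 degrees of freedom:

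- n = 50, d = 0.25: non-centrality 0.25 × √25 = 1.25, critical t 1.984, power 0.236.
- n = 40 (20% loss), d = 0.25: non-centrality 1.118, power 0.197.
- n = 53 (the table's 159), d = 0.25: power 0.247, so meeting Table 3 would not repair this claim.
- n = 252 gives 0.7998 and n = 253 gives 0.801, so 253 per arm are needed.
- At n = 50, power reaches 0.80 at d = 0.566. Even d = 0.50 gives only 0.697.

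**The case against.** The arithmetic is not in dispute. Four points can be made on the other side.

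*The 150/159 gap is small.* With complete data it costs about 2 points of power and looks like rounding to 50 per arm. This stands as a matter of size. Taken alone it would be a minor correction, and the weight of the point comes from the missing allowance for loss and from the SOA–TOA claim.

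*The loss rates are not the trial's.* This is correct. They are illustrative, and the active follow-up measures may keep loss low. But with no loss at all, 150 still misses the stated β.

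*The planned analysis is not a one-way ANOVA.* The Data analysis section specifies repeated measures ANOVA at three months. If this is treated as a test of change from baseline, the effective f² is 0.0625/[2(1 − ρ)], where ρ is the baseline–follow-up correlation. Omnibus power at N = 150 then passes 0.80 at a ρ between 0.52 and 0.53. At ρ = 0.6 it is 0.87, or 0.78 with 20% loss. Below ρ = 0.5 it is lower than the one-way figure. So it cannot be said that the trial will certainly have less than 80% omnibus power, only that the calculation it cites does not show 80%. The article gives no correlation and does not size on one.

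This argument does not rescue the SOA–TOA claim. At an assumed ρ = 0.6, power for d = 0.25 at 50 per arm is 0.28 for a change score (d/√0.8 = 0.280) and 0.34 with baseline adjustment (d/√0.64 = 0.3125). Reaching 80% by baseline adjustment would need ρ of about 0.90.

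*Declaring a null SOA–TOA result inconclusive in advance goes too far.* This is fair. The interpretation should rest on the confidence interval, so that sentence is optional.

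**Conclusion.** The concern holds. The target of 150 is 9 below the size required by the calculation cited for it, and that size makes no allowance for loss. On that calculation 150 gives 0.780 with complete outcomes, and 0.68 to 0.54 if 20% to 40% of outcomes are missing. Those loss rates are assumptions for illustration. The more serious error is that 80% power is stated for a SOA–TOA difference of d = 0.25, where 50 per arm gives about 24%. The difference between d = 0.25 in the text and f = 0.25 in Table 3 explains the gap. The 24% assumes a two-sided 0.05 comparison of follow-up values with complete data. No plausible correlation that the article supports would bring it near 80%. The power statement must be corrected, because a central comparison would otherwise be read against a power the trial does not have.

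**What to change.** Keep 150 and correct the Power calculation section:

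1. State that 150 randomised (50 per arm) gives power 0.78 for the three-group test at f = 0.25 with complete data. Add that power would be about 0.68, 0.61 or 0.54 with 20%, 30% or 40% loss, marked as illustrative unless the sponsor has a rate of its own.
2. Replace the SOA–TOA claim: about 24% power for d = 0.25, and 80% power for d of about 0.57, in a two-sided comparison of 50 with 50.
3. Make it explicit that f in Table 3 and d in the text are different measures, and have the table and text show the same N.
4. Optionally, add that a non-significant SOA–TOA result will be interpreted from its confidence interval and not as evidence of no difference.

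This costs wording only and needs no further participants. The price is a less favourable power statement. Raising recruitment to 159 would close the first gap if nobody were lost, but would leave the SOA–TOA power at about 25%, so the second correction is needed in either case.

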### Randomization

After the t0 measurement is completed, participants are allocated to one of the three trial arms. Because this randomized clinical trial is internet-based, we will organize the allocation procedures online as well. As the number of participants we aim to include in each trial arm (*n *= 50) is not very large, random variation in baseline characteristics could reduce group equivalence. Online, server-based performance of randomization procedures comes with the advantage of being able to implement stratified allocation or allocation through adaptive randomization relatively easy.

To prevent between-group variability on relevant baseline characteristics, we use an adaptive or biased-coin randomization algorithm for this trial. Adaptive randomization aims to ensure trial arms are balanced with respect to a priori defined participant factors as well as for the number of participants in each group. Simulation studies show that adaptive randomization provides better balanced trial arms when compared with 'normal' randomization [35] and that it is more efficient in balancing multiple poli-level factors than permutated block stratification [36]. Although not widely used due to organizational complexity, adaptive randomization is a highly effective allocation method, and its wider adaptation in the conduct of randomized clinical trials is recommended [37]. The use of adaptive randomization is supported in the CONSORT statement [38]. We will implement the Pocock & Simon Range Method of adaptive randomization [39], with D = 'range', G is the sum of D (no factor weighting), and P = 0.60.

